### Measurement tools

In this study, the commercially available, evidence-based measurement tools described below will be used. These outcome measures will be done every 2 weeks for a period of 2 months.

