**Methods/design:**

This study is a single-centre, single (assessor)-blinded, randomised control trial in patients with burns donor sites to their thighs. Patients will be randomly allocated to a control group (with no compression to donor sites) or to an experimental group (with compression to donor sites) as the comparative treatment. Groups will be compared at baseline regarding the important prognostic indicators: donor site location, depth, size, age, and time since graft (5 days). The IPG treatment will be administered post-operatively (on day 5). Follow-up assessments and garment replacement will be undertaken fortnightly for a period of 2 months.

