### Intervention

The treatment will be IPG objectively measured in millimetres of mercury using the PicoPress® pressure sensor (mediGroup Australia, Melbourne, Australia) [29], and it will be administered post-operatively between days 3 and 5. Participants in the treatment group will be asked to wear the IPG for 23 h/day for a period of 8 weeks. Individual wear time for the IPG will be established through completion of a daily log book for the treatment group. Participants will commence involvement in the study as inpatients on the burn ward and may progress to the outpatient clinic during the study as per normal hospital procedure. Once discharged from the inpatient burn ward, participants will return to the hospital for fortnightly study measurements. Both groups will be reviewed every 2 weeks over the 2-month period to check scar and/or IPG quality (in millimetres of mercury). Surgical intervention, wound care dressings, medication, nutrition, exercise and nursing management of the donor site will be standardized between groups, the sole difference being that one group will have compression therapy for their donor site and the other will not.

The principal investigator will record demographic information, including age, skin type (as assessed using Fitzpatrick skin typing) [30], cause of injury, TBSA burned, depth of injury, surgical procedure undertaken, medication used and time taken to heal (including number of dressing changes and types of dressings used). Smoking status (which may impact on wound healing) will also be recorded. The donor will be considered healed when there is no raw, open or oozing epithelium. A second researcher blinded to the intervention will complete all outcome measures.

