#### Conclusion of assessments

For participants in the IPG group, the principal researcher will measure the amount of pressure in each garment and issue new interim garments if needed, thereby ensuring that pressure remains constant. This concludes the assessment and treatment regime. The participant will undergo the same regime at each subsequent appointment for the period of 8 weeks. At this point, they will be released from the study.

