### Proposed data analysis

Groups will be compared at baseline regarding the important prognostic indications: donor site location, depth, size, age, skin type and time since graft. Data will be entered into IBM SPSS 22.0 for Windows software files (IBM, Armonk, NY, USA) and tested for normality of distribution. Descriptive statistics for all variables will be computed. If parametric statistics are able to be used, a two-way analysis of variance for group × time interaction will be performed to compare skin thickness between normal, donor and scar sites with a planned least significant difference post hoc analysis. Significance will be set at *p* < 0.05. If raw data are not normally distributed, an equivalent non-parametric analysis will be used [40].

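### The named test for skin thickness is the group × time interaction, but the trial is sized for a plain between-group difference and no reading before the garment is stated

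*Protocol article*

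**What the plan says.** Under Sample size, the protocol article takes a minimum clinical difference of 0.5 mm between groups, SD 0.5 mm and power 0.9, and arrives at 22 per group. That is the sizing of a simple comparison of two means.

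Under Proposed data analysis, the named test is different: "a two-way analysis of variance for group × time interaction will be performed to compare skin thickness between normal, donor and scar sites", followed by a planned least significant difference post hoc analysis. The text adds "Significance will be set at *p* < 0.05". The analysis is named for skin thickness only.

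On timing, Measurement tools says "These outcome measures will be done every 2 weeks for a period of 2 months". The Intervention section says of the garment that "it will be administered post-operatively between days 3 and 5", while the abstract gives day 5. The abstract also says "Follow-up assessments and garment replacement will be undertaken fortnightly for a period of 2 months".

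On baseline, Proposed data analysis says "Groups will be compared at baseline regarding the important prognostic indications: donor site location, depth, size, age, skin type and time since graft". Erythema, pain and scar score are not in that list, and depth is not defined. Conclusion of assessments says "The participant will undergo the same regime at each subsequent appointment for the period of 8 weeks", which implies an earlier appointment but does not place it before or after the garment is put on.

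**The concern.** The sample size and the named test address different quantities. The sizing asks whether the arms differ by 0.5 mm. The interaction asks whether that difference changes from one measured visit to the next.

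The mismatch matters little if a reading before the garment is among the visits, because the arm difference is then expected to be zero at the start and any later effect appears as change. It matters a great deal if every visit is on treatment. A benefit that arises in the first fortnight and then persists is constant over the visits, and a constant difference contributes nothing to the interaction. The Background puts re-epithelisation at about 14 days, so the first fortnightly reading falls near wound closure, and part of any effect may be present by then.

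At stake is the result of the test the protocol names. It could be non-significant although the garment achieves the full difference for which the trial was sized.

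**Working it through.** **Inputs from the protocol article.** Sample size: difference 0.5 mm, SD 0.5 mm, power 0.9, n = 22 per group. Proposed data analysis: significance level 0.05, taken here as two-sided. Measurement tools: fortnightly visits for 2 months, read here as weeks 2, 4, 6, 8 (k = 4), with week 0 added as the alternative (k = 5).

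**Assumptions not in the documents.** Within-patient correlation ρ from 0.3 to 0.8, equal variance at all visits, compound symmetry, no dropout. Three profiles for the arm difference d_t at weeks 2, 4, 6, 8, each reaching 0.5 mm at week 8:
- constant: 0.50, 0.50, 0.50, 0.50
- 70% at week 2: 0.35, 0.40, 0.45, 0.50
- 50% at week 2: 0.25, 0.33, 0.42, 0.50

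**Step 1. The plan's own figure.** n per group = 2(z₀.₉₇₅ + z₀.₉₀)² × SD²/δ² = 2(1.960 + 1.282)² × 0.25/0.25 = 21.01, rounded up to 22. A two-sample t test with 22 per group has power 0.900. The stated 22 reproduces, as the sizing of a single between-group difference. Each profile reaches 0.5 mm at week 8, so the week-8 comparison has 90% power in all three.

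**Step 2. Interaction, on-treatment visits only.** Noncentrality λ = (n/2) × Σ(d_t − d̄)² / [SD²(1 − ρ)], with 3 and 126 degrees of freedom and critical F 2.68.
- Constant: Σ(d_t − d̄)² = 0, so λ = 0 and power equals the significance level, 5%, at every ρ.
- 70% at week 2: d̄ = 0.425 and the sum of squares is 0.0125. At ρ = 0.6, λ = 11 × 0.0125/(0.25 × 0.4) = 1.375 and power is 14%.
- 50% at week 2: the sum of squares is 0.0347. At ρ = 0.6, λ = 11 × 0.0347/0.1 = 3.82 and power is 33%.

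**Step 3. Group main effect, same visits.** λ = (n/2) × d̄² / {SD²[1 + (k − 1)ρ]/k}, with 1 and 42 degrees of freedom and critical F 4.07. Constant effect at ρ = 0.6: the variance of a patient's mean is 0.25 × 2.8/4 = 0.175, λ = 11 × 0.25/0.175 = 15.7 and power is 97%.

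**Step 4. Interaction with a week-0 visit added (d = 0 there).** Constant effect: the sum of squares is 0.20. At ρ = 0.6, λ = 11 × 0.20/0.1 = 22 with 4 and 168 degrees of freedom (critical F 2.43), and power is 97%.

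**Power over ρ = 0.3 to 0.8**

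| Profile | Interaction, weeks 2–8 | Interaction, week 0 added | Main effect, weeks 2–8 | Week-8 difference |
|---|---|---|---|---|
| Constant | 5% | 81% to >99% | 99.7% down to 94% | 90% |
| 70% at week 2 | 10% to 25% | 70% to 99.9% | 98% down to 85% | 90% |
| 50% at week 2 | 20% to 62% | 66% to 99.8% | 94% down to 75% | 90% |

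A simulation of the constant profile (4,000 runs, ρ = 0.5) gave interaction power 0.050 without and 0.929 with the week-0 visit, in agreement with the formula.

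**The case against.** The article is a summary of a fuller protocol, and a visit table is commonly left to that document. Visits every two weeks can mean weeks 0, 2, 4, 6, 8. The abstract speaks of a baseline comparison with time since graft of 5 days, the day on which it also starts the garment. The reference to subsequent appointments implies a first one, and baseline depth could be an ultrasound reading, since the DermaScan section is headed as a depth assessment. This stands. A reader might infer that no reading before the garment will be taken; the documents show only that none is stated.

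A reader might also infer that an effective garment would be reported as having no effect. That goes too far. The low power belongs to one term. The same two-way analysis yields a group main effect with ample power for a constant effect, and a post hoc analysis is planned. Nor would a missing baseline make the comparison invalid: under randomisation a between-arm comparison after treatment is unbiased, and its test already allows for chance imbalance. A baseline adds precision.

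The constant profile is the extreme case. Thickness may keep diverging as the scar matures, which the article puts at 18–24 months, and the interaction then sees part of the effect. The gain from a week-0 visit in the interaction test also assumes that an early open wound correlates with later scar as strongly as later visits do with each other, which is untested. Finally, the analysis is named for thickness, so nothing is shown for erythema or pain.

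What remains is that the article itself names the interaction and not the between-arm difference. The mismatch with the sizing is in the text and does not depend on an unshown document.

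**Conclusion.** The concern holds as a mismatch between the sizing and the named test, made worse by a schedule that does not say whether thickness is read before the garment is applied. If the visits are weeks 2, 4, 6 and 8, the interaction has 5% power for a 0.5 mm effect complete at week 2 and 10–25% when 70% is present by then. The between-arm difference at week 8 keeps the planned 90%, and the main effect has 94–99.7% for the constant effect.

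These figures rest on 22 per group and SD 0.5 mm from the protocol, and on assumed correlations of 0.3–0.8, compound symmetry and the effect profiles shown. If a week-0 reading is in fact among the visits, the loss for the constant profile largely disappears (81% or more), though the named test still differs from the one used for sizing. The conclusion concerns thickness. For erythema and pain, a time-0 reading would improve precision but is not required for a valid comparison.

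**What to change.** 1. In Proposed data analysis, name the between-arm difference in thickness at week 8 as the effect tested, so that it matches the 0.5 mm sizing. The group main effect over the visits is an alternative, but it loses power if the effect builds up gradually (75–94% in the 50% profile). Keep the interaction as a secondary description of the time course.
2. In Measurement tools, state the visit weeks and fix a time-0 set of readings with the existing devices and scar scale, at the same review in both arms and before garment issue where wound contact is acceptable. Use it as a baseline covariate.
3. Reconcile the start of the garment between the abstract and the Intervention section, so that time 0 is defined relative to one stated point.

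The first and third changes are wording only. The second costs a few minutes of extra measurement at an existing review. Trial status reports eight pilot participants recruited and 44 required, so the changes can still take effect.

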#### Scar depth assessment

The DermaScan C (Cortex Technology, Hadsund, Denmark) is a high-frequency, high-resolution ultrasound scanner which objectively captures and reproduces skin thickness. It can clearly discriminate between hypertrophic scar, normal scar and normal skin and is evidenced as having high inter-rater/intra-rater reliability [31, 32].

#### Erythema assessment

The DSM II ColorMeter (Cortex Technology) is a self-contained, battery-operated device which provides objective measurements of erythema and melanin based on the light absorption characteristics of human skin [33, 34].

#### Garment pressure assessment in mmHg

The PicoPress® pressure sensor has been clinically tested for validity and reproducibility in objectively measuring the pressure in millimetres of mercury of compression garments. It has been shown to be an adequate and reliable instrument for use [29, 35].

#### Subjective scar assessment

The Patient Observer Scar Assessment Scale has been shown to consistently demonstrate valid and reliable measures of scar quality [36]. It is a simple and cost-effective assessment that reports the patient’s opinions of the scar, including pain, itch, colour, stiffness, thickness, irregularity and overall appearance, and the observer assessment of pigmentation, thickness, relief, pliability, surace area, height, vascularity and overall appearance of the scar [36–39].

#### Conclusion of assessments

For participants in the IPG group, the principal researcher will measure the amount of pressure in each garment and issue new interim garments if needed, thereby ensuring that pressure remains constant. This concludes the assessment and treatment regime. The participant will undergo the same regime at each subsequent appointment for the period of 8 weeks. At this point, they will be released from the study.

### Standardization

Considerations to standardize each measurement will include the following:Measurement of the donor site with the garment removed for a specific length of time (5 minutes)Temperature-controlled roomPosition of donor anatomy dermatome location L3–L5 anterolateral thighA template on the donor site to identify the area to be measuredTime of day when measured

### Sample size

Previous studies using the DermaScan C have shown an effect size of 2.35 (1.69–3.01) between skin-thickness measurements of donor sites and scar sites [22]. For a minimum clinical difference of 0.5 mm between groups of less than 0.05 and a power of 0.9, 22 subjects per group would be required [22, 40] (assuming a standard deviation of 0.5 mm for wound thickness).

On the basis of data obtained from January 2013 to May 2015 (where patients admitted to the RBWH [name] Adult Burns Centre are represented as males = 593 admissions and females = 237 admissions), the ratio is expected to be 3:1. This ratio should accurately reflect the distribution of burns within the general community.

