## Background

Thickened erythematous scars can reduce physical function and create a distorted physical appearance for a burn-injured patient [1–3]. When a burn penetrates deeply enough into the dermis of the skin, surgery is often required to assist healing. The surgery involves removing the burned or dead skin (debriding) and replacing it with a thin section of unburned healthy skin (donor skin), known as a split-thickness skin graft (SSG). This donor skin is surgically removed, commonly from the patient’s own thigh area, using a dermatome at a measure of 8/1000 inch to 12/1000 inch (depending on the thickness required to heal the burn defect) and includes the epidermis and the upper third of the dermis [4, 5]. The tissue removed for a SSG is comparable in depth to a partial thickness skin loss [5]. The remaining exposed area of dermis is referred to as the *donor site*. The donor skin is then placed over the original debrided burn wound area to assist in healing. There are sufficient residual epidermal cells in the remaining dermis to allow re-epithelisation to occur over an approximately 14-day period [4]. The donor site wounds discussed in this paper are routinely dressed with ALGISITE, ACTICOAT, MELOLIN, and HYPAFIX (all from Smith & Nephew, Andover, MA, USA) and heavy crepe bandage immediately post-operatively until wound review day 3 or 5. After this time, the donor site is then dressed with soft white paraffin (Kenkay Pharmaceuticals, Smeaton Grange, NSW, Australia), Xeroform (DeRoyal, Powell, TN, USA), and HYPAFIX or heavy crepe bandage until the wound is considered healed (no raw, open or oozing epithelium). Interim pressure garments (IPGs) for donor sites are routinely provided to inpatients at the [name] Burns Centre, as early as day 1 post-operatively with a focus on securing wound dressings rather than scar management.

Despite the donor site depth being extremely thin, patients often describe this new wound to be like ‘bad gravel rash’ and report worse pain in this wound than at the original burn or graft site. Pain associated with burn surgery has been shown to delay patients’ return to work and daily functional activity, with donor sites consistently identified as a potential source of concern for burn patients [1–3, 6–8]. Protection and support of the remaining epidermal and dermal elements of this surgical wound (donor site) are required to assist effective tissue healing with minimal scarring [4, 5, 9–12].

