### Trial status

Eight participants have been recruited to date for a pilot study. A total of 44 participants (22 for each group) is required.

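### The 22 per group is correct for 90% power but leaves no room for loss, and the total required is set at the same 44; the 2.35 effect size quoted beside it is a different contrast

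*Protocol article*

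**What the plan says.** The Sample size section of the protocol article first reports an effect size of 2.35 (1.69–3.01) from previous studies with the same ultrasound scanner, "between skin-thickness measurements of donor sites and scar sites". It then sizes the trial on different inputs:

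- Difference: "For a minimum clinical difference of 0.5 mm".
- Spread: "assuming a standard deviation of 0.5 mm for wound thickness".
- Significance level: the wording is garbled ("between groups of less than 0.05"), but Proposed data analysis makes the meaning clear: "Significance will be set at *p* < 0.05".
- Result: "and a power of 0.9, 22 subjects per group would be required".

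Trial status, directly after reporting that eight people have been recruited for a pilot, states: "A total of 44 participants (22 for each group) is required".

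The Intervention section has participants return to hospital every two weeks after discharge, over 8 weeks in all. The article states no expected loss and no addition to the sample for it.

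**The concern.** A sample size formula gives the number of patients who must contribute data to the comparison. Here the same number is the total the trial is said to require. If the calculation has no slack, every patient lost between the ward and the last visit comes out of the stated power.

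The second issue is the 2.35. It stands at the head of the section that justifies the sample size, so a reader may take it as evidence that a large effect is expected. The trial compares garment with no garment, both on donor sites. A difference between two kinds of tissue does not tell us the size of that effect.

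The power statement will matter if the result is null. The Discussion says that a finding of no difference would inform spending on scar management. How far a null result can carry that weight depends on the power actually delivered.

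**Working it through.** **Inputs.** Difference 0.5 mm, standard deviation 0.5 mm and power 0.90 are from Sample size. The level of 0.05 is from Sample size and Proposed data analysis. Sidedness is not stated; two-sided is assumed because it reproduces the 22 (one-sided 0.05 gives 18). Loss rates of 10%, 15% and 20% are assumptions.

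**Step 1: reproduce the stated figure.** The standardised difference is d = 0.5 / 0.5 = 1.0.

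- Normal approximation: n = 2 × (1.960 + 1.282)² / d² = 21.01, rounded up to 22 per group.
- Two-sample t-test: n = 22.02 per group. Power at 22 per group is 0.8997.

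The stated 22 is reproduced, and 2 × 22 = 44 agrees with Trial status.

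**Step 2: slack.** By the t-test there is none: 22.02 are needed and 22 are planned. By the normal approximation, power is 91.3% at 22 per group and 89.98% at 21, so the slack is about one patient per group.

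**Step 3: power if 44 are recruited and some are lost.** Number left per group = 22 × (1 − loss), with d = 1.0 and two-sided 0.05:

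| Assumed loss | Left per group | Power, t-test | Power, normal approximation |
|---|---|---|---|
| 0% | 22.0 | 90.0% | 91.3% |
| 10% | 19.8 | 86.5% | 88.2% |
| 15% | 18.7 | 84.5% | 86.4% |
| 20% | 17.6 | 82.1% | 84.3% |

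Unrounded, the t-test values are 0.8655, 0.8447 and 0.8211, or about 87%, 84% and 82%.

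**Step 4: recruitment that would keep 90%.** n / (1 − loss), rounded up:

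- 10%: 22 / 0.90 = 24.4, so 25 per group (50 in total).
- 15%: 22 / 0.85 = 25.9, so 26 per group (52 in total).
- 20%: 22 / 0.80 = 27.5, so 28 per group (56 in total).

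**Step 5: is 2.35 an input?** With d = 2.35 the t-test needs 5 per group (normal approximation 4). With its lower limit, 1.69, it needs 9 (normal approximation 8). Neither gives 22. The 22 comes from 0.5 / 0.5 alone.

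**Step 6: what covariate adjustment could recover.** Proposed data analysis compares normal, donor and scar sites, so normal-skin thickness appears to be measured. If it correlates r with the outcome within groups, the effective standardised difference becomes 1 / √(1 − r²). At 18 per group, where the unadjusted power is 83.0%:

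| Assumed r | Effective d | Power |
|---|---|---|
| 0.2 | 1.021 | 84% |
| 0.3 | 1.048 | 86% |
| 0.4 | 1.091 | 89% |
| 0.5 | 1.155 | 92% |

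The article gives no value of r. Only the top of this range brings power back to 90%.

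**The case against.** **The arithmetic is sound.** This stands. The 22 is correct for its inputs, and the point concerns what is promised from it.

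**The loss is the reviewer's assumption, and the effect is small.** Both are true. The article gives no rate, and 20% loss still leaves 82% power. A condensed article may also leave an allowance for loss to the full protocol, or may mean 44 as the number analysed. Even so, the article itself gives the calculated number and the total required, and they are identical. The sentence giving the total follows one about recruitment, so a reader will take it as the recruitment target.

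**The planned analysis is not a t-test.** Proposed data analysis names a two-way analysis of variance for group by time, and no single visit is designated as the comparison. The powers above are therefore for a simple two-group comparison, which is what the stated inputs describe. They are not the power of the planned model.

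**The 2.35 is labelled openly and changes nothing numerically.** Also true. It is described as donor versus scar sites and is not used in the calculation. What remains is a point of clarity about its placement.

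**A stronger reading that does not hold.** A reader might set the 0.5 mm target against the harvest depth in Background ("using a dermatome at a measure of 8/1000 inch to 12/1000 inch", that is, 0.203 to 0.305 mm) and infer that the target is implausible because it exceeds the whole layer removed. The documents do not support this. The outcome is skin or scar thickness by ultrasound, and one stated aim is to reduce scar thickness or height. A raised scar can be thicker than the layer removed, so harvest depth does not cap the difference between groups. Low power below a declared minimum clinical difference is also no error in itself. Nor does the article give any basis for supposing a standard deviation above 0.5 mm.

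**Conclusion.** The point holds in a limited form. The sample size is correctly calculated, but the stated 90% power is reached only if all 44 participants are analysed. With 10% to 20% loss it is about 87% to 82%, a shortfall of roughly 3 to 8 percentage points. This rests on assumed loss rates, a two-sided 0.05 level, the article's own 0.5 mm difference and standard deviation, and a simple two-group comparison.

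Separately, the 2.35 gives the calculation no support. It is a donor-versus-scar contrast and had no part in producing 22.

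A reader might go further and conclude that the trial is seriously underpowered or that its target is unattainable. The article supports neither conclusion: power stays above 80% across the loss range examined if the stated difference and standard deviation are right.

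**What to change.** 1. In Sample size, state that 22 per group gives 90% power only if all 44 participants are analysed, and that with an assumed 10–20% loss it is about 82–87% for a simple two-group comparison. State that the 0.05 level is two-sided, if that is what was used.
2. Remove the 2.35, or say that it describes donor versus scar sites, is not the expected garment effect and did not enter the calculation.
3. Optionally, adjust the group comparison for the patient's own normal-skin thickness, specified before the data are seen. Present this as something that may recover part of the loss (84–92% at 18 per group for correlations of 0.2–0.5), with no promise of restoring 90%.

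Items 1 and 2 cost a few sentences and a slightly less favourable power figure. Item 3 should need no extra measurement if normal skin is scanned as the analysis section implies. None needs more patients. If the sponsor prefers to keep 90% under loss, the alternative is to recruit 50 to 56 in total for 10–20% loss, which is 6 to 12 more than planned.
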